### Randomization

The study employs a block randomization by station derived from a computer-generated random number table. Blocks of two study packages are assigned to each ambulance vehicle/aircraft. Paramedics are blinded to the treatment assigned until package opening. A field logistics research coordinator is responsible for randomization compliance at the vehicle level through daily checks. Compliance at the patient will be verified through the randomization number of the product label and recorded on the data checklist.

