### Setting

The trial setting is the city of Toronto with a population of at 2.5 million served by an emergency medical services system employing approximately 430 Advanced Life Support Paramedics, 570 Basic Life Support Paramedics and 3,000 Firefighter first responders under the same medical direction. In addition, the trial includes one Ornge Transport Medicine rotor wing base with two helicopters and 32 critical care flight paramedics providing responses from accident scenes outside the city of Toronto within south central Ontario. Enrolled patients will be directly admitted to two adult designated regional Trauma Centers.

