### Intervention Protocol

All patients will be treated according to research medical directives (Additional File 2) based on a standardized provincial out of hospital trauma treatment protocol [6]. The study solution is started within 4 hours of the time the emergency call was received at ambulance dispatch. Samples of peripheral blood will be collected upon emergency department (ED) arrival, 12, 24 and 48 hours after ED arrival from a vein remote from the venous access site for the study infusion. Blood samples will be collected in heparinized and non-additive vacutainers by a single trained lab technician and immediately (within 1-h) shipped to a single designated laboratory for whole blood flow cytometric cellular analyses and measurement of circulating molecular immuno-inflammatory markers. Serum will be frozen for subsequent analyses. Whole blood will be incubated with saturating concentrations of the adhesion (CD62L-FITC, CD11b-PE), degranulation (CD66b-FITC, CD63-PE), apoptotic/necrotic (Annexin V-PE, 7-AAD, Active Caspase-3, CD95-Fas, CD178-FasL) markers, in conjunction with CD14-APC surface staining (to differentiate leukocyte subsets). Results will be acquired on a Becton Dickinson dual-laser (488 nm and 635 nm) BD FACSCalibur flow cytometer using CellQuest software. Serum samples will be analyzed for pro-/anti-inflammatory cytokines (TNF-α, IL-10), soluble leukocyte and endothelial-derived adhesion molecules (sICAM-1, sVCAM-1, sE-selectin, sL-selectin), pro-/anti-apoptotic molecules (sCD95, sCD95L, TNF-RI, sFas/FasL) and neuro-biomarkers of brain injury (S100B, NSE, MBP) (Additional File 3).

Magnetic Resonance Imaging on a 1.5 Tesla General Electric Signa Magnet is planned for completion at 4 months for consenting patients using a standardized protocol (Additional File 4, 5, 6, 7); a 3D 1.3 mm thick, T1-weighted, series (TE 4-2, TR 35, flip angle 35), an interleaved 3 mm thick PD and T2-weighted spin echo sequence (TE 39/80, TR 3000, flip angle 90) (Additional File 6), a gradient echo sequence and Diffusion Tensor Imaging (11 directions) (Additional File 7); tissue segmentation and parcellation including lesion quantification [7-12] using previously published in-house software as well as ANALYZE software [7,13].

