### Analysis Plan

This is a feasibility study of two year's duration with a projected screening of 130 patients and recruitment of 100. The primary outcome measure, change in the proportion surviving 30 days post trauma between the treatment and control groups, will be analyzed by means of a generalized linear mixed model which included covariates of interest. The two groups are not expected to be different at baseline, and it is hypothesized that the treatment group would show a 20% decrease in mortality at 30 days post trauma whereas the control group would remain unchanged. To derive a reduced subset of risk factors for the predictor models, acceptable model building strategies are planned (i.e. dropping variables showing extremely small variability and those found to be highly correlated (i.e. correlation coefficient ≥0.8)). Treatment and time factors will be analyzed using a generalized linear mixed models of the secondary outcome repeated measures: the change in mortality after discharge over time as well as the neurocognitive and neuropsychological outcome summary scores. For secondary outcome analyses, the alpha will be adjusted to account for multiple comparisons. Where there is more than one measure for a neuropsychological test (e.g., processing speed, working memory, visuospatial, language, verbal memory, non-verbal memory - with the exception of executive processes, since different measures relate to different brain regions), a composite or prototypical measure will be derived from group comparison. Serial changes in all secondary immune modulation measures, neuro-biomarkers, neurocognitive and neuropsychological outcomes, and structural imaging measures will be evaluated by two-way ANOVA for repeated measures. All analysis will be conducted blinded to treatment assignment.

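### The two-way repeated-measures ANOVA for the serial immune, neuro-biomarker and imaging measures leaves out the station and vehicle blocking; if the stratum is prognostic, reported standard errors are somewhat too wide.

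*Protocol article*

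**What the plan says.** **Design.** Under Randomization, the protocol article states: "The study employs a block randomization by station derived from a computer-generated random number table". It adds: "Blocks of two study packages are assigned to each ambulance vehicle/aircraft". Under Setting, all air enrolment comes from a single rotor-wing base with two helicopters, "providing responses from accident scenes outside the city of Toronto". Blocking by station therefore makes air service a stratum of its own.

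**Analysis.** The Analysis Plan gives three model statements:

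- 30-day survival "will be analyzed by means of a generalized linear mixed model which included covariates of interest". Neither the covariates nor the random effects are named.
- "Treatment and time factors will be analyzed using a generalized linear mixed models of the secondary outcome repeated measures". This covers mortality after discharge and the neurocognitive and neuropsychological summary scores.
- Serial changes in the immune measures, neuro-biomarkers, neurocognitive and neuropsychological outcomes, and "structural imaging measures will be evaluated by two-way ANOVA for repeated measures".

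The neurocognitive and neuropsychological outcomes thus appear under both the second and the third statement. The measures tied to the ANOVA alone are the immune, neuro-biomarker and imaging measures. No station, vehicle or land/air term is named anywhere in the section.

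**The concern.** When allocation is balanced within strata and the strata predict the outcome, the difference between arms varies less from trial to trial than under simple randomisation. An analysis that ignores the strata leaves the between-stratum variance in its residual, so the reported standard error describes a less precise design than the one used. Intervals come out too wide and tests too conservative.

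For the mixed models this could be settled by a covariate or random effect listed in a fuller document. For the ANOVA it is different, because the article fixes a form with two factors. The ANOVA sentence does not name them. Treatment and time is the natural reading, since the purpose is serial change between arms and the same paragraph pairs those two factors for its other repeated-measures model.

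The stratum could plausibly matter for the blood markers. Air crews attend scenes outside the city, and the start of infusion has a wide window: "The study solution is started within 4 hours of the time the emergency call was received at ambulance dispatch". Sampling is timed from Emergency Department arrival, so one sample label can stand for different times since injury and infusion. With "projected screening of 130 patients and recruitment of 100", before deaths and losses to follow-up, there is little information to spare.

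**Working it through.** **Inputs from the article.** 100 patients; blocks of two packages per vehicle or aircraft; one air base with two helicopters.

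**Assumptions.** The article gives no air share, air-land difference, number of stations or land vehicles, alpha level or power. I assume an air share p of 0.1 to 0.3, an air-land difference d of 0.5 to 1.0 within-stratum SD, a two-sided 5% test, one package per arm in each block, and an effect that an unblocked design of this size would detect with 80% power (2.80 = 1.96 + 0.84). No figure stated in the plan can be reproduced on this point.

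**Formulas.**

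- Share of variance due to the stratum: R² = p(1−p)d² / (1 + p(1−p)d²)
- Reported SE / true SE for the unadjusted analysis: 1/√(1−R²)
- True alpha of the unadjusted test: 2[1 − Φ(1.96/√(1−R²))]
- Power, unadjusted, blocked design: Φ((2.80 − 1.96)/√(1−R²)). Blocking shrinks the true SE, but the test still uses the inflated one.
- Power, adjusted: Φ(2.80/√(1−R²) − 1.96)

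| p, d | p(1−p)d² | R² | SE ratio | True alpha | Power unadjusted | Power adjusted | Gain (points) |
|---|---|---|---|---|---|---|---|
| 0.1, 0.5 | 0.0225 | 0.022 | 1.011 | 4.8% | 80.2% | 80.8% | 0.6 |
| 0.2, 0.8 | 0.1024 | 0.093 | 1.050 | 4.0% | 81.1% | 83.6% | 2.5 |
| 0.3, 1.0 | 0.2100 | 0.174 | 1.100 | 3.1% | 82.2% | 86.9% | 4.6 |

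**Check by simulation.** Each setting had 4,000 trials of 100 patients, permuted blocks of two within 4, 10, 40 or 80 strata, a continuous outcome and no treatment effect. The strata carried 0 to 20% of the variance (assumed).

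| Stratum share of variance | Reported / true SE, unadjusted | Type I error, unadjusted |
|---|---|---|
| 0 to 5% | 0.975 to 1.03 | 0.042 to 0.059 |
| 10% | 1.02 to 1.08 | 0.036 to 0.046 |
| 20% | 1.06 to 1.10 | 0.033 to 0.039 |

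The first row is mostly simulation noise around no effect. With fixed stratum effects, type I error was 0.042 to 0.056 throughout.

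At a 10% share, the true SE of the estimate was the same with or without adjustment for 10 strata (0.188 and 0.188). Fixed stratum effects made it worse for 40 strata (0.186 rising to 0.195) and for 80 strata (0.194 rising to 0.228), because about 20 and 37 strata respectively ended on an incomplete block.

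**Limit of the check.** One time point stands in for the between-patient treatment comparison. A stratum difference that is constant over time cancels from the treatment-by-time test, so these figures do not apply to that test.

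**The case against.** **The generalized linear mixed models.** A reader might infer that every stated analysis ignores the blocking. The article does not support that. The survival model has unnamed covariates and random effects. With one binary result per patient, a random effect would ordinarily need a grouping above the patient, and station is an obvious candidate. A condensed article may leave such lists to a fuller document. This objection stands, and for these models there is no shown error.

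**Direction and meaning of the loss.** A reader might also infer that the blocking's precision is thrown away or that conclusions become unsafe. Neither follows. Blocking has already reduced the true variance of the estimate; only its reported standard error is too wide, and the error is conservative.

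**Size of the gain.** It is tempting to set adjusted power of up to 87% against 80%, or to read 100/(1−R²) = 102 to 121 as patients gained. Both treat the unadjusted comparator as unblocked. In the blocked design the unadjusted test already reaches about 80.2% to 82.2%, so the gain is at most about 4.6 points.

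**Is the stratum prognostic?** The 4-hour window applies to all patients, and nothing says that air patients start or arrive later. Prognostic strength is therefore an assumption. With a stratum share of 5% or less, the simulation shows essentially no effect.

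**Reach.** These are secondary measures in a feasibility study. The article says that baseline survival rates will inform the definitive trial; it does not say that biomarker standard errors will. The magnitudes above are for a continuous marker and say nothing about survival.

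What remains is that the ANOVA, as fixed, has no place for a feature of the randomisation.

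**Conclusion.** The point holds for the two-way repeated-measures ANOVA of the serial immune, neuro-biomarker and imaging measures, reading its factors as treatment and time. It is clearest for the blood markers, which are sampled repeatedly; the Intervention Protocol plans the MRI at 4 months.

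If station or land/air service predicts the outcome, reported standard errors are about 1% to 10% too large over the assumed range, and a nominal 5% test of the treatment comparison runs between about 4.8% and 3.1%. Adjustment is worth about 0.6 to 4.6 points of power. If the stratum is not prognostic, the effect is near zero. Type I error is not inflated in any material way. It is a small matter, worth correcting because the method is stated and the change costs almost nothing.

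**What to change.** In the Analysis Plan:

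1. For the immune, neuro-biomarker and imaging measures, replace the two-way repeated-measures ANOVA with a linear mixed model containing treatment, time, treatment-by-time and a parsimonious randomisation-stratum term. That term is a land/air indicator, plus a random intercept for station if it can be estimated. Do not use vehicle-level fixed effects, which can cost more precision than they recover.
2. Exempt the stratum term from the variable-reduction rule. Its criterion of very small variability could remove an indicator that is mostly land.
3. State that the generalized linear mixed models carry the same term. This is for consistency and does not correct a shown error. It would also help to say which model governs the neurocognitive and neuropsychological outcomes, now listed under both.
4. State a fallback: drop the station intercept and keep land/air if the model does not converge.

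The cost is analysis wording and one or two degrees of freedom. Land and air have separate prehospital case report forms, so service type should be available. The article says that the randomization number is recorded but not that it identifies the station, so that link should be confirmed. The number of stations is not given, so whether a station intercept is stable with 100 patients is unknown; hence the fallback.

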### Ethical Considerations

We received waiver of consent approval in accordance with the Tri-Council Policy Agreement http://www.pre.ethics.gc.ca/english/policystatement/policystatement.cfm. We will seek consent from the surviving patients or the families of non survivors to analyze the blood results of all randomized patients. An itemized consent will be used where appropriate to record simultaneously consent for all follow up tests and evaluation of surviving patients.

## Discussion

The metaanalysis by Wade et al[1] suggested TBI was the cohort of patients most likely to demonstrate significant changes with HSD resuscitation. This study is designed to test the feasibility of randomizing patient in the prehospital setting to this cohort of patients and explore through additional tests, the important immunological, serum markers, structural changes and neuropsychological and neurocognitive outcomes in addition to the traditional survival outcomes.

We anticipate three aspects of the trial will present challenges to trial success; ethical demands, challenging follow up and comprehensive accurate timely data collection of patient identifiers and clinical or laboratory values. The ethical considerations are probably the most challenging as we will have to secure consent to analyze the blood of non survivors from families who have suffered an unexpected and devastating loss through trauma.

Additionally, we are concerned that many patients will be lost to follow up as individuals who survive TBI may be unable to return to their previous address or place of occupation and are very dependent on family. If important links to the family are not established during the first hospitalization and maintained post discharge we may be unable to find all the patients. In addition, the structural and neurocognitive and neuro psychological tests require a return visit to hospital. This may place additional demands on the family and care giver who may be overwhelmed given the functionality of some traumatic brain patients.

Finally, we anticipate two types of patients will provide unique challenges to data collection: those who die in the Emergency Department and those who met the Glasgow Coma Scale criteria for enrolment however this finding was attributed to drugs or alcohol rather than brain injury and they were discharged from the Emergency Department within hours of the accident. Strategies are in place to address these issues a priori in advance of the trial. Those who die soon after arrival in the Emergency Department often require the coroner's intervention and traditionally the charts are instantly sequestered by the coroner's staff. They commonly are unidentified and therefore it will be hard to find their health care advocate who can consent to using their blood and outcome data up until their death. We hope to overcome this with an agreement in principle with the provincial coroner to allow access to the chart at the coroner's office. We have developed a working practice with the coroner's office to confirm identification and next of kin data at the time of body retrieval

We anticipate the patients who met the GCS eligibility criteria based on alcohol consumption and are discharged relatively quickly from the Emergency Department will be hard to track down. There will be insufficient time to identify them correctly or confirm their demographic information and next of kin prior to discharge and follow up of the non brain injured group will be challenging. We will use a hierarchical approach to find these patients including government health care billing number, police report, Emergency Department report, Ambulance call report, web based telephone listings, newspapers which identify the individual based on the notoriety of the event. In addition, each receiving hospital had an active trauma registry which tracked the patients to conduct a functional evaluation at 30 days post-discharge. The surgical investigators have offered to confirm identification and obtain consent in their outpatient clinics if the patients return for follow up. This may prove to be helpful as many of these patients require forms completed by the physician for return to work, disability, insurance etc.

This study incorporates several unique features which may be helpful to subsequent trials. It is a feasibility design that follows a rigorous published methodology. It evaluates the feasibility of the out of hospital randomization as well as the inhospital data capture and analysis of complicated critical care variables, immunological markers, CT and MRI studies, and neurocognitive evaluation. The data capture forms appended to this document had to be created by the investigators as none could be found in the literature despite numerous studies in a similar cohort of patients. This should save others time and permit a more standardized data capture for future trials should they prove useful when reviewed by our peers. We hope providing the methodology will encourage others to test the feasibility of a randomized controlled trial before implementation in the complicated and costly out of hospital arena.

## Abbreviations

ICU: Intensive Care Unit; CT: Computerized Tomography; MRI: Magnetic Resonance Imaging; All other short forms are written in full with first use.
